## Abstract

**Background:**

In primary care, up to 74% of physical symptoms is classified as unexplained. These symptoms can cause high levels of distress and healthcare utilization. Cognitive behavioral therapy has shown to be effective, but does not seem to be attractive to patients. An exception herein is a therapy based on the consequences model, which distinguishes itself by its labeling of psychosocial distress in terms of consequences rather than as causes of physical symptoms. In secondary care, 81% of the patients accepts this therapy, but in primary care the outcome is poor. We assume that positive outcome can also be reached in primary care, when the consequences model is modified and used bottom-up in an easily accessible group training, in which patients are relieved of being blamed for their symptoms. Our aim is to investigate the (cost-)effectiveness of this training.

**Methods and design:**

A randomized controlled trial is designed. One hundred patients are randomized to either the group training or the waiting list.

Physicians in general practices and outpatients clinics of general hospitals refer patients. Referral leads to inclusion if patients are between 18 and 65 years old, understand Dutch, have no handicaps impeding participation and the principal DSM-IV-TR classification is undifferentiated somatoform disorder or chronic pain disorder. In contrast to other treatment effect studies, the co-morbidity of a personality disorder does not lead to exclusion. By this, we optimize the comparability between the study population and patients in daily practice enlarging the generalization possibilities.

Also in contrast to other effect studies, we chose quality of life (SF-36) instead of physical symptoms as the primary outcome measure. The SF-6D is used to estimate Quality Adjusted Life Years (QALYs). Costs are measured with the Trimbos/iMTA Questionnaire for Costs associated with Psychiatric Illness. Measurements are scheduled at baseline, after the training or waiting list, three and twelve months after the training. The differences between measurements are analyzed according to the intention-to-treat principle. The cost-effectiveness is expressed as costs per QALY, using multiple sensitivity analyses on the basis of a probabilistic model of the trial.

**Discussion:**

If we show that our group training is (cost-)effective, more patients could be served, their quality of life could be improved while costs might be reduced. As the training is investigated in a heterogeneous patient group in the daily practice of a mental healthcare institution, its transfer to practice should be relatively easy.

**Trial registration:**

Nederlands Trial Register, NTR1609

## Background

The estimated prevalence of unexplained physical symptoms in primary care ranges from 18 to 74% [1,2]. This huge difference in estimating prevalence is caused by multiple definitions of unexplained physical symptoms such as Unexplained Physical Symptoms (UPS), Medical Unexplained Physical Symptoms (MUPS), functional somatic syndromes and abridged somatization. We use the Diagnostic and Statistical Manual of Mental Disorders IV -Text Revision (DSM-IV-TR) [3] and define unexplained physical symptoms with the classification of 'undifferentiated somatoform disorder' and 'chronic pain disorder'. In the Netherlands, the estimated prevalence of unexplained physical symptoms in primary care is 18% [2]. Most of these unexplained physical symptoms can be classified as a somatoform disorder, of which 13.0% meets the criteria of undifferentiated somatoform disorder and 1.6% meets the criteria of chronic pain disorder [4]. In general, the DSM-IV-TR classifies symptoms without making assumptions about etiology. However, the DSM-IV-TR does presume psychological causes in the beginning, severity, increase or continuation of pain in chronic pain disorder. Therefore, we prefer to use the mere descriptive term 'Unexplained Physical Symptoms (UPS)', which corresponds with the DSM-IV-TR terms 'undifferentiated somatoform disorder' and 'chronic pain disorder' with the exception of the assumptions about etiology.

Patients with UPS have high levels of psychosocial distress and healthcare utilization [5], for which cognitive behavioral therapy is shown to be most effective [6-9]. However, it is widely believed, that patients with unexplained physical symptoms reject this kind of therapy. The consequences model is a positive exception. The key difference of this model compared to other cognitive behavioral models is its labeling of psychosocial distress in terms of consequences rather than as causes of UPS. Herewith, the consequences model fits both professionals' and patients' point of view. Refraining from labeling psychosocial distress as causes of UPS corresponds with the lack of consensus among professionals about the causes of UPS, which is reflected in the ongoing debate about the position of somatoform disorders on Axis I or III in the next edition of Diagnostic and Statistical Manual of Mental Disorders [10,11]. Moreover, labeling psychosocial distress as consequences, matches the patients' perspective of UPS. This is reflected in the fact, that 81% of the patients in academic medical care accepts an individual therapy based on the consequences model [12] and this individual therapy has positive outcomes in secondary care [13]. Unfortunately, in primary care, this high acceptance rate could not be reproduced and resulted in poor outcome [2,14].

We assume that the consequences model can maintain its positive outcome for patients in primary care, when we make some modifications. Firstly, we tailor this model more accurately to patients' perspective of their physical symptoms. Moreover, we put additional attention to relieve patients from being blamed for their symptoms. Furthermore, we make the group training easy accessible. Our aim is to investigate the (cost-)effectiveness of this easily accessible group training for patients in primary care conducted in the daily practice of our mental healthcare institution, Riagg Rijnmond, The Netherlands. This study protocol provides a detailed description of the cognitive behavioral group training and the design of the randomized controlled trial investigating the (cost-)effectiveness of this training.

### Objectives

The primary aim of this study is to investigate (cost-)effectiveness of our easily accessible protocollized group training for patients with UPS in primary care conducted in the daily practice of a mental healthcare institution. The secondary aim is to identify (personality-)variables enabling to predict this (cost-)effectiveness.

## Methods and design

### Design

The (cost-)effectiveness of the group training is evaluated in a randomized controlled trial (see Figure 1).

**Figure 1 F1:**
[figure not shown]
**Design of the randomized controlled trial**.

The study started February 2005. The inclusion of patients has ended in September 2008. The one-year follow-up period of the randomized patients will be finished in April 2010.

### Study population

Patients are included when:

1. they are between 18 and 65 years old;

2. they are able to speak, read and write Dutch;

3. their UPS persists at least 6 months;

4. their UPS is classified as undifferentiated somatoform disorder or chronic pain disorder according to the criteria of the Structured Clinical Interview for DSM-IV Axis I Disorders/Patient edition (SCID-I/P) [15].

Patients are excluded when:

1. UPS is not the principal somatic disease;

2. undifferentiated somatoform disorder or chronic pain disorder is not the principal DSM-IV-TR classification;

3. handicaps like cognitive mental impairment and/or blindness impending the patient to participate in the training.

To optimize the comparability between the study population and the patients with UPS in daily practice and to make generalization to daily practice possible, we have decided that having a personality disorder is not an exclusion criterion; this is in contrast to other treatment effect studies. We do measure personality disorder with the self-report questionnaire for DSM-IV Axis II personality disorders (VKP) based on the International Personality Disorder Examination (IPDE) [16]. By measuring personality disorders using this instrument, we can not only describe the study population in terms of personality disorders, but also identify the influence of personality disorders on (cost-)effectiveness.

Patients are recruited from general practices and outpatient clinics of general hospitals in and nearby Rotterdam, the Netherlands. Physicians' attention is drawn to the group training by periodical postcards informing them when and how they can refer patients to the group training. Patients' attention is drawn to the group training by announcements in local newspapers and on websites of patients' associations, in which they are asked to make an appointment with their physician to discuss referral when interested. Physicians decide whether the physical symptoms are medically explained or unexplained hereby checking the first exclusion criterion, after which they refer patients when they find this appropriate. After referral, patients are invited for an interview, preferably in a medical setting, in which they are verbally and in writing informed about the study. In this interview, the first three inclusion criteria and the last exclusion criterion are verified. After receiving patients' signed informed consent, patients are invited for a second interview, in which the last inclusion criterion and the second exclusion criterion are investigated by the Structured Clinical Interview for DSM-IV Axis I Disorders/Patient edition (SCID-I/P) administered by independent psychologists. These psychologists make the final decision based on the results of the SCID-I/P whether patients' UPS can be classified as an undifferentiated somatoform disorder or as a chronic pain disorder and whether this disorder is the principal DSM-IV-TR classification. If undifferentiated somatoform disorder or chronic pain disorder is the principal DSM-IV-TR classification, then patients complete the self-report questionnaire for DSM-IV Axis II personality disorders (VKP).

Right before the start of each next training, the newly included patients fill in the questionnaires. Subsequently, an independent statistician randomizes them to either the group training or waiting list with a computer-based 1:1 ratio randomization procedure. The results of this randomization procedure are sent to the patient by letter. If randomization leads to starting with the group training, then an invitation for the group training is enclosed in the randomization letter. After the group training or after a waiting-period of the same length as the group training, all patients fill in the questionnaires for the second time.

After filling in the outcome measurements for the second time, the patients on the waiting list are invited to the group training. They follow the group training after their waiting period together with the newly included patients randomized to the group training in the most recent randomization. For patients on the waiting list, a longer waiting period is not feasible, because the study is conducted in the daily practice of a real life mental healthcare institution. By combining the patients assigned by the previous randomization to the waiting list with the patients assigned by the next randomization to the group training in the same training, the patients in both conditions receive exactly the same training. After completing the training, all patients fill in follow-up measurements after three months and after one year.

### Experimental condition: group training

The group training [17] is based on the consequences model, which labels psychosocial stress as consequences rather than as causes of UPS to prevent the suggestion that 'its all in the head'. The original consequences model [18] assumes that UPS induces irrational beliefs regarding the symptoms resulting in consequences, which maintain or increase UPS (see black arrows in Figure 2). Its implementation in an individual therapy starts with beliefs labeling them as irrational, disputing them and replacing them with rational ones. Subsequently, other consequences are changed to break the vicious circle [19]. The ultimate goal is to reduce physical symptoms.

**Figure 2 F2:**
[figure not shown]
**Modified consequences model based on Speckens et al**. [18,19].

We assume that this original consequences model has not completely succeeded in preventing the 'its all in the head' suggestion. After all, patients might perceive the focus on irrational beliefs still as 'its all in the head'. Patients might experience the disputing of these beliefs as blaming and belittling. Blaming and belittling result in a rejection of the therapy by patients and in poor outcome [20,21]. That is why we modify the consequences model for our group training (see red arrows in Figure 2). Our group training focuses on the visible consequences, labeling them as survival strategies in reaction to physical symptoms, justifying their existence by their benefit in short term, albeit indicating their harmfulness in the long run and therefore replacing them with long run beneficial strategies. Subsequently, the underlying beliefs of these survival strategies are explored, checked and, if necessary, changed in more helpful ones. Finally, the problem-solving model of Nezu *et al*. [22] is introduced to facilitate developing personal effective survival strategies for all kinds of problems, acknowledging that physical symptoms can increase the number of problems. The ultimate goal is not aimed at reducing physical symptoms as with the original consequences model, but is aimed at improving quality of life.

In summary, the group training uses the consequences model bottom-up instead of the commonly used top-down approach. By using the consequences model bottom-up (starting with consequences and unconditionally accepting and justifying their existence) instead of top-down (starting with addressing irrational beliefs and disputing them), we reach a closer match with the patients' physical point of view. Moreover, patients are relieved from being blamed, called exoneration, by justifying the existence of consequences by their benefit in short term, by which we facilitate compliance. Furthermore, we tailor the setting of the training to patients' physical point of view by organizing the training in a medical healthcare setting and not in our own mental healthcare institution. Herewith, also the implicit but unintended 'its all in the head' suggestion is avoided.

This bottom-up strategy results in a group training comprising thirteen ad verbatim protocollized weekly sessions of two hours each.

After session 1, the structure of each session is as follows:

• sharing experiences of the past week;

• discussing home-assignments;

• doing a group breathing and relaxation exercise;

• identifying short-term beneficial survival strategies and modifying them into long-term beneficial ones;

• ending with a summary of the session and new home-assignments.

Each session is built around a theme. In session 1, trainees get acquainted with each other by telling each other about their symptoms and by setting their personal goals for the training.

In session 2, the flight-fight cycle and habits in reaction to symptoms are identified as survival strategies of the body and modified with the learning of the breathing and relaxation exercise and the reshaping of habits into long-term beneficial ones.

In session 3, avoidance and overactivity in reaction to symptoms are identified as survival strategies of the body and modified by scheduling different kinds of activities in a feasible pace alternated with short breaks (5 to 10 minutes) that is compatible with the trainees' physical condition.

In session 4, emotions in reaction to symptoms are identified as useful survival strategies indicating the need for problem-solving. Moreover, the physical symptoms of emotions are notified and reduced or even relieved with the breathing and relaxation exercise.

In session 5, thoughts in reaction to symptoms are identified as survival strategies of the mind and, if necessary, modified with the Ellis' ABCDE scheme into more helpful ones.

In session 6, a good physical shape is identified as an effective survival strategy of the body, which can be achieved by doing a low cardiac physical activity (like walking or biking) twice a day and increasing this up to a maximum of 60 minutes twice a day, after which physical shape can be maintained by a regular sport twice a week.

In session 7, the form at Figure 2 is filled in by the trainees and discussed afterwards with an important and trusted person in his or her own social environment.

In sessions 8 to 12, the five steps of the problem-solving method (problem-attitude, problem-definition, alternative solutions, solution plan, solution implementation and evaluation) are identified and practiced.

In session 13, a personal First Aid Kit is composed out of the learned long-term beneficial survival strategies aimed to prevent relapse.

### Control condition: waiting list

Patients assigned to the waiting list condition, wait during the group training of 13 weeks, after which they start with their training.

### Outcome measurements

(Cost-)effectiveness is measured with three self-report questionnaires, which are sent to patients' home to be completed before randomization, at the end of the training or waiting list period, after 3 and 12 months after the training (see Figure 1).

1) Short Form Health Survey (SF-36) [23]

The SF-36 measures functional health and well-being during the past four weeks with the following eight multi-item scales: Physical functioning, Role functioning physical, Bodily pain, General health, Vitality, Social functioning, Role functioning emotional and Mental health. The scores of the SF-36 can also be summarized in the Mental and the Physical summary scores [24]. Furthermore, a utility score can be derived from 11 items of the SF-36. These 11 items define six dimensions of health, the SF-6D; Physical functioning, Role limitations (Role functioning physical in combination with Role functioning emotional), Bodily pain, Social functioning, Vitality and Mental health. The outcome of the SF-6D can be converted into Quality Adjusted Life Years (QALYs), the preferred outcome in health economics, using formerly called 'valuations studies' [25].

2) Symptom Checklist Revised (SCL-90-R) [26]

The SCL-90-R measures a broad range of symptoms and their intensity during the past week with the following eight multi-item scales: Phobic anxiety, Anxiety, Depression, Somatization, Obsessive-compulsive, Interpersonal sensitivity, Hostility and Sleep difficulties. The scores of the SCL-90-R can be summarized in the Global severity index, reflecting the overall psychological distress.

3) Trimbos/iMTA Questionnaire for Costs associated with Psychiatric Illness (TiC-P) [27]

The TiC-P measures direct medical costs due to healthcare utilization during the past four weeks, excluding the group training itself. The costs of the training itself are calculated using the records of the institution. The TiC-P also registers the indirect non-medical costs due to productivity loss during the past two weeks. This second part of the questionnaire about indirect costs is based on the short form of the Health and Labour Questionnaire (HLQ).

### Outcome measurements: clinical evaluation

The aim of the clinical evaluation is to investigate the effectiveness of the group training by comparing the improvement of quality of life gained in the training group to the one in the waiting list group. Primary outcome measure is the Mental and Physical summary score of the SF-36. Secondary outcomes are the eight individual scales of the SF-36 and the scales of the SCL-90-R.

### Outcome measurements: economic evaluation

The aim of the economic evaluation is to investigate cost-effectiveness of the group training in terms of cost per Quality Adjusted Life Years (QALYs). QALYs are estimated by converting SF-6D into utilities by means of the preference-based UK tariff [25]. Indirect costs for employed patients are measured with the TiC-P by the reported duration of sick leave and the production loss without sick leave. The indirect costs of production loss due to sick leave are computed by multiplying the number of sick leave's day with the average net income per worker related to age and gender. By a long-term sick leave, the friction-cost method is applied to assess the productivity loss, using a friction period of 5 months.

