### Statistical analyses: economic evaluation

The economic evaluation is conducted from a societal perspective, the preferred perspective in health economic evaluations [29]. This means that all costs are included: the direct medical costs, the indirect medical costs and the indirect costs associated with productivity loss of patients. Adopting a societal perspective also means that all relevant effects and all costs beyond the time frame of the trial should be measured. In this case, the differences between group training and waiting list can only be measured empirically till 13 weeks, but relevant effects and costs might occur beyond that artificial time horizon. For this reason, we will estimate effects and costs till 2 years, using a Markov model [30]. By making the Markov model probabilistic, we will be able to implement multiple sensitivity tests simultaneously and test for specific model assumptions. A critical assumption will be the extrapolation of the effect beyond 13 weeks. This assumption will be explored by calculating the minimal duration that the group training should be effective, in order to achieve a satisfactory level of cost-effectiveness.

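### Sick-leave days are priced at net income, which undervalues lost output under the declared societal perspective

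*Protocol article*

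**What the plan says.** Under *Statistical analyses: economic evaluation* the protocol article states: "The economic evaluation is conducted from a societal perspective, the preferred perspective in health economic evaluations". It then spells out the scope: "This means that all costs are included: the direct medical costs, the indirect medical costs and the indirect costs associated with productivity loss of patients".

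Under *Outcome measurements: economic evaluation* it describes how lost work is measured and priced:

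- Two components are measured in employed patients: "the reported duration of sick leave and the production loss without sick leave".
- Sick leave is costed as the number of days absent times "the average net income per worker related to age and gender".
- For long-term absence, "the friction-cost method is applied to assess the productivity loss, using a friction period of 5 months".

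No price is given for the second component, lost output while at work. No separate daily price is given for days inside the friction period. The TiC-P collects "indirect non-medical costs due to productivity loss during the past two weeks" (*Outcome measurements*). On sensitivity analysis, the article plans several within a probabilistic model and singles out one assumption: "A critical assumption will be the extrapolation of the effect beyond 13 weeks". The wage price is not mentioned among them.

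**The concern.** When an employee is absent, society loses the output of that day. The usual proxy for its value is what the labour costs in full: the gross wage plus employer contributions. Net income is only the part that reaches the worker. Tax and premiums move money from one party in society to another and do not make the lost output smaller. Net income therefore suits a patient or household perspective, not the one the article declares.

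Cost-effectiveness is part of the primary aim (*Objectives*), and cost per QALY is the economic outcome. The price also enters the 2-year Markov model and the calculation of how long the training must stay effective to be worth its cost. With all else equal, if the training reduces sick leave, an underpriced day makes that required duration come out too long. If the training increases sick leave, it comes out too short. The clinical primary outcome, the SF-36 summary scores, is not touched.

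**Working it through.** The article gives no wage, tax or contribution figure, so there is no figure of its own to reproduce. The direction follows from algebra; the size needs assumptions.

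**Inputs from the article.** Perspective: societal. Price of a sick-leave day: net income by age and gender. Friction period: 5 months.

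**Assumed inputs.** t, the share of gross pay taken as employee tax and premiums: 20%, 30%, 40%. e, employer contributions as a share of gross pay: 0%, 15%, 25%.

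**Step 1: price ratio.** With gross wage W, net income is W(1 - t) and full labour cost is W(1 + e). So

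k = net price / full labour cost = (1 - t)/(1 + e),

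which is below 1 whenever t or e is positive.

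**Step 2: numbers.** The understatement is 1 - k, and the full-cost value is 1/k times the planned one.

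| t | e | k | Understated by | 1/k |
|---|---|---|---|---|
| 20% | 0% | 0.80/1.00 = 0.800 | 20% | 1.25 |
| 20% | 15% | 0.80/1.15 = 0.696 | 30% | 1.44 |
| 20% | 25% | 0.80/1.25 = 0.640 | 36% | 1.56 |
| 30% | 0% | 0.70/1.00 = 0.700 | 30% | 1.43 |
| 30% | 15% | 0.70/1.15 = 0.609 | 39% | 1.64 |
| 30% | 25% | 0.70/1.25 = 0.560 | 44% | 1.79 |
| 40% | 0% | 0.60/1.00 = 0.600 | 40% | 1.67 |
| 40% | 15% | 0.60/1.15 = 0.522 | 48% | 1.92 |
| 40% | 25% | 0.60/1.25 = 0.480 | 52% | 2.08 |

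The rows with e = 0 compare net income with the gross wage alone.

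**Step 3: difference between arms.** Let S be the difference in sick-leave cost (training minus waiting list) at full labour cost, and R the difference in all other costs. The full-cost total is R + S; the planned total is R + kS. The sick-leave part shrinks by the factor k whatever its sign. It does not cancel because both arms share the price. This assumes one k for everyone. If tax shares differ by age and gender, k applies within each age and gender group.

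**Step 4: total difference.** Take assumed amounts with k = 0.60 and R = +1000:

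- S = -500: full-cost total 1000 - 500 = +500; planned total 1000 - 300 = +700, further from zero.
- S = +500: full-cost total 1000 + 500 = +1500; planned total 1000 + 300 = +1300, closer to zero.

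The total can move either way.

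**Step 5: does anything in the plan correct the price?** The friction-cost method limits how long an absence is counted and states no different price per day. No sensitivity analysis on the price is stated.

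**The case against.** The strongest reply is that the two sections do not strictly contradict each other. The article defines its perspective by the cost categories it covers, and productivity loss is covered. That lost output should be priced at full labour cost is a costing principle, which the article does not itself state. This is fair. The point is a poor fit between price and perspective, not a clash between two sentences. It still stands, because a net price leaves out part of the value of the output that the perspective is meant to count.

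A second reply is that net income may be an imprecise label for a tariff in the costing sources, which are not available here. That is possible, but nothing in the article supports another reading, and an analyst who follows the text would use take-home pay. The price is a stated rule, so it is not a detail that the article leaves to a fuller document.

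A third reply is that the consequence is limited: only employed patients contribute, recall covers two weeks, and the controlled comparison ends at 13 weeks. This limits the weight of the point but does not remove it, because the model carries costs to 2 years.

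A reader might infer two stronger things that the article does not support:

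- **That all productivity costs are understated by the same percentage.** The net price is attached only to sick-leave days. None is stated for reduced output at work, and its use inside the friction period is an inference from the absence of any other price.
- **That the cost difference between arms is biased towards zero.** This holds for the sick-leave part only. The total also contains training and medical costs.

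**Conclusion.** The concern holds for sick-leave days. As written, the rule prices them below their value to society whenever income tax, employee premiums or employer contributions are positive. That direction depends on no figure from the trial.

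The size cannot be taken from the article. The range of about 20% to 52%, or full-cost values 1.25 to 2.08 times the planned ones, rests wholly on the assumed rates. It applies to the sick-leave cost in each arm and to the sick-leave part of the difference. The size and sign of the effect on cost per QALY cannot be known in advance, since they depend on the sick-leave difference and on the other cost components. The price should be changed, but it does not threaten the clinical comparison.

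**What to change.** In *Outcome measurements: economic evaluation*:

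- Replace net income with average gross labour cost (gross wage plus employer contributions) by age and gender as the price of a sick-leave day, and say that it also applies to days counted within the friction period.
- State the same price for output lost while at work.
- Keep net income, if at all, as a labelled sensitivity analysis.
- If the intended tariff is already a gross labour-cost figure, correct the wording and name the tariff.

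The cost is one unit price in the costing program, or a few words if only the label is wrong. No new patient data are needed.
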